**Figure: 4 Sample size calculation.**

The total sample size is 66 persons. The sample size is 22 persons per each group.

$$\text{Drop out} = 20\% = 4.4 = 5$$

Therefore, the number of sample size of each group was 27 subjects. The sample size of this study is set to 30 persons per group. The purpose of this setting is to further improve the inspection performance (Power value). Substitute 30 samples per group into the G Power calculation program to derive a higher performance value (Power value). So each group will select 30 sample sizes.

### **3.4 Intervention method**

#### **3.4.1 Bafa Wubu Tai Chi group**

The simplified Tai Chi Bafa Wubu Tai Chi (Eight Methods and Five steps) newly compiled by the State Sports General Administration in 2019 is adopted. Instructors who have more than 5 years of teaching experience and have a Tai Chi teaching qualification certificate conduct instructed exercises. Including 16 action content, as shown in the following table:

- |                                                                                                                                                                                                                                                                                                                                                                                                                                                                                                                                                                                                                                                                                                                                                                                                                                                                                                                                                                                               |
|-----------------------------------------------------------------------------------------------------------------------------------------------------------------------------------------------------------------------------------------------------------------------------------------------------------------------------------------------------------------------------------------------------------------------------------------------------------------------------------------------------------------------------------------------------------------------------------------------------------------------------------------------------------------------------------------------------------------------------------------------------------------------------------------------------------------------------------------------------------------------------------------------------------------------------------------------------------------------------------------------|
| 
 
1) Start up
 
2) Left squeeze; Right squeeze; Left squeeze; Double press
 
3) Right picking potential; Left pressing potential; Left elbow potential; Right holding potential
 
4) Right-handed posture; Left-handed posture; Right squeezed posture; Double press posture
 
5) Left picking position; Right pressing position; Right elbow position; Left holding position
 
6) Progress and control the situation
 
7) Retreat
 
8) Move left and squeeze left; Move left and double press
 
9) Move right and squeeze right; Move right and double press
 
10) Retreat and take the left and right
 
11) Progress controls the situation
 
12) Step right, right elbow, right step, right leaning
 
13) Move left and left elbow position; Move left and hold left position
 
14) Independence
 
15) Cross hands
 
16) Close up
 
 |
|-----------------------------------------------------------------------------------------------------------------------------------------------------------------------------------------------------------------------------------------------------------------------------------------------------------------------------------------------------------------------------------------------------------------------------------------------------------------------------------------------------------------------------------------------------------------------------------------------------------------------------------------------------------------------------------------------------------------------------------------------------------------------------------------------------------------------------------------------------------------------------------------------------------------------------------------------------------------------------------------------|

#### **3.4.2 Traditional He-style Tai Chi group**

Using the "He-Style Tai Chi Pu" published by the People's Sports Publishing House of China in 2003. Instructors who have more than 5 years of teaching experience and have a Tai Chi teaching qualification certificate conduct instructed exercises. This traditional He-style Tai Chi consists of 72 movements, as shown in the table below.

|                                                                                                                                                                                                                                                                                                                                                                                                                                                                                                                                                                                                                                                                             |                                                                                                                                                                                                                                                                                                                                                                                                                                                                                                                                                                                                                                                                                                            |                                                                                                                                                                                                                                                                                                                                                                                                                                                                                                                                                                                             |
|-----------------------------------------------------------------------------------------------------------------------------------------------------------------------------------------------------------------------------------------------------------------------------------------------------------------------------------------------------------------------------------------------------------------------------------------------------------------------------------------------------------------------------------------------------------------------------------------------------------------------------------------------------------------------------|------------------------------------------------------------------------------------------------------------------------------------------------------------------------------------------------------------------------------------------------------------------------------------------------------------------------------------------------------------------------------------------------------------------------------------------------------------------------------------------------------------------------------------------------------------------------------------------------------------------------------------------------------------------------------------------------------------|---------------------------------------------------------------------------------------------------------------------------------------------------------------------------------------------------------------------------------------------------------------------------------------------------------------------------------------------------------------------------------------------------------------------------------------------------------------------------------------------------------------------------------------------------------------------------------------------|
| Start
1) Three pairs of King Kong
2) Lazy tie
3) Like closed like closed
4) Single whip
5) The leader of the King Kong
6) White crane spreads its wings
7) diagonal
8) Pipa momentum
9) Leap and go diagonally
10) Turn around pipa pose
11) Jump with arms around knees
12) Fuhu
13) Finger thumping
14) Look at the fist at the bottom of the elbow
15) Fallen Monkey
16) White crane spreads its wings
17) diagonal
18) Seabed needle
19) Flashback
20) Like closed like closed
21) Single whip
22) Cloud Hands
23) High Detective Horse
24) Pat your feet left and right
25) Rotate the heel | 26) Two steps and three beats
27) Qinglong Exploring the Sea
28) Second kick
29) Separate horseshoes and tuck the knees
30) Magpies
31) Harrier stand up
32) Left and right knee wraps
33) Cover your hands
34) Hold your head and push the mountain
35) Like closed like closed
36) Single whip
37) Before and after move
38) Remainder
39) Mustang split mane
40) Jade Girl Shuttle
41) Turn around lazy tie
42) Like closed like closed
43) Single whip
44) Cloud Hands
45) Die Cha
46) Sweep the legs
47) Golden Rooster Independent
48) Double shaking feet
49) Fallen Monkey
50) White Crane Spreading Wings
51) diagonal | 52) Seabed Needle
53) Flashback
54) Like closed like closed
55) Single whip
56) Cloud Hands
57) High Detective Horse
58) Single swing foot
59) Slinging finger crotch pounding
60) King Kong
61) Lazy tie
62) Right tie seven stars
63) Looking back at the painting
64) Huanglong stirring water
65) Like closed like closed
66) Single whip
67) Left tie seven stars
68) Progressive cross hand
69) Regress and Stride Tiger
70) Double swing feet
71) Move the bow and shoot the tiger
72) Three pairs of King Kong
Close |
|-----------------------------------------------------------------------------------------------------------------------------------------------------------------------------------------------------------------------------------------------------------------------------------------------------------------------------------------------------------------------------------------------------------------------------------------------------------------------------------------------------------------------------------------------------------------------------------------------------------------------------------------------------------------------------|------------------------------------------------------------------------------------------------------------------------------------------------------------------------------------------------------------------------------------------------------------------------------------------------------------------------------------------------------------------------------------------------------------------------------------------------------------------------------------------------------------------------------------------------------------------------------------------------------------------------------------------------------------------------------------------------------------|---------------------------------------------------------------------------------------------------------------------------------------------------------------------------------------------------------------------------------------------------------------------------------------------------------------------------------------------------------------------------------------------------------------------------------------------------------------------------------------------------------------------------------------------------------------------------------------------|

### 3.4.3 Control group

Because the control group does not do any exercise intervention, during the 12-week experiment, all participants will be asked to keep normal diet and daily routine.

### 3.4.4 Warm-up and cool-down before and after the intervention

Warming up before intervention can increase the muscle temperature, increase muscle and tendon elasticity, and prevent sports injuries. Cooling exercises after intervention can reduce muscle soreness and quickly restore physical strength. In this study, static stretching will be used for warm-up and cooling content before and after the intervention. The static stretching content comes from the book "Warm-Up and Stretching" written by Ian Jeffreys, MS in 2008. 15 static stretching actions are selected. They are: 1) Rotation of the neck to the right/left. 2) Neck flexion and Neck extension. 3) Stretching the triceps. 4) Stretching the upper back. 5) Stretching the upper back and forearms. 6) Stretching the lower back and sides. 7) Stretching the low back from a seated position. 8) Stretching the hip flexors. 9) Stretching the sides, triceps, and upper back. 10) Stretching the hamstrings. 11) Stretching the hamstrings and lower back. 12) Stretching the hamstrings and hip adductors. 13) Stretching the hamstrings, hip adductors, and lower back. 14) Stretching the hip adductors. 15) Stretching the calves. In the warm-up and cooling process, each stretching action is required to reach the

individual's best state for at least 30 seconds in order to achieve the effect of stretching.  
Achieve beneficial warm-up before intervention and body recover after the intervention.

### **3.5 Intervention time**

The Bafa Wubu Tai Chi group and the traditional He-style Tai Chi group will receive Tai Chi training 12 weeks, 3 times a week, each course is 60 minutes, including 30 minutes of Tai Chi exercises and 15 minutes of warm-up and cold down. The control group will have 1 health lecture every month, 3 times in total 12 weeks. During the 12-week experiment, all participants will be asked to keep normal diet and daily routine.

### **3.6 Data collection**

Visit 1 (Baseline): Before the test, all participants performed basic personal physical sign evaluation and filled out the personal physical sign evaluation form. The evaluation content included gender, age, body height, body weight, and BMI value.

Visit 2 (Pre-training): All participants will participate in blood lipid assessment (TC, TG, LDL-C, HDL-C), physical fitness assessment (Body mass, BMI, fat percentage, muscle content, flexibility, upper and lower limbs Strength, balance and aerobic endurance).

Visit 3 (Post-training): All participants will be participated in the examination as same as the assessment of visit 2.

### **3.7 Outcome measurements**

#### **3.7.1 Primary outcome measures**

##### **1) Body composition**

Measures of body composition variables include: body weight, BMI, fat percentage, muscle content.

Measuring instrument: Body composition analyzer (BCA-2Atype). Place of Origin: produced by China Tongfang Health Technology Company (Beijing).

Measuring place: Physical Fitness Testing Center of Tai Chi Sports Center, Jiaozuo City, China. The assessment is conducted by a qualified assessor.

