### 3.3 Sample size

The purpose of this study is to evaluate the effect of the newly compiled Bafa Wubu simplification Tai Chi and traditional He-style Tai Chi on the blood lipids and physical fitness of overweight college students. Therefore, using a randomized controlled trial study design (RCT). Since blood lipids are the main outcome variable of the study, however, the previous research literature did not have 3 groups of test subjects similar to this research, similar exercise intensity and similar parameters. Therefore, G Power 3.1.9.4 is used to estimate the sample size. Since the experiment is designed into three groups, select "ANOVA: Fixed effects, omnibus, one-way" in F tests, select "A priori: Compute required sample size" in Analysis, and set the effect size conventions to the maximum value  $f=0.40$ ,  $\alpha$  err prob is set to 0.05, power ( $1-\beta$  err prob) value is set to 0.80, Number of groups is set to 3. The calculation steps are as follows:

The screenshot shows the G\*Power 3.1.9.4 software window. The 'F tests' tab is selected, and the 'ANOVA: Fixed effects, omnibus, one-way' test is chosen. The 'Analysis' section is set to 'A priori: Compute required sample size'. The 'Input' parameters are: Effect size  $f = 0.40$ ,  $\alpha$  err prob = 0.05, Power ( $1-\beta$  err prob) = 0.80, and Number of groups = 3. The 'Output' parameters are: Noncentrality parameter  $\lambda = 10.5600000$ , Critical F = 3.1428085, Numerator df = 2, Denominator df = 63, Total sample size = 66, and Actual power = 0.8180744. The 'Test family' is 'F tests' and the 'Type of power analysis' is 'A priori: Compute required sample size - given  $\alpha$ , power, and effect size'. The 'Input Parameters' section shows 'Determine =>' with 'Effect size f' set to 0.40, ' $\alpha$  err prob' set to 0.05, 'Power ( $1-\beta$  err prob)' set to 0.80, and 'Number of groups' set to 3. The 'Output Parameters' section shows 'Noncentrality parameter  $\lambda$ ' set to 10.5600000, 'Critical F' set to 3.1428085, 'Numerator df' set to 2, 'Denominator df' set to 63, 'Total sample size' set to 66, and 'Actual power' set to 0.8180744. A 'Calculate' button is visible at the bottom right.

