##### **2) Blood lipid**

Measures of blood lipid variables include: total cholesterol (TC), triglyceride (TG), low-density lipoprotein cholesterol (LDL-C) and high-density lipoprotein

cholesterol (HDL-C).

Measuring instrument: CardioChek PA Blood Analyzer. Place of Origin: USA

Measuring place: The Physical Fitness Testing Center of Jiaozuo People's Hospital, Jiaozuo City, China. Due to the particularity of blood lipid measurement, the measurement and evaluation will be completed by a qualified nurse.

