### **3.8.2 Data analysis**

Data will be collected by means of Excel 2019, statistical analysis will be carried

out using the IBM SPSS version 26.0 (IBM Corporation, NY, USA). Data will be present as mean  $\pm$  standard deviation (SD), and 95% confidence interval (CI) adopted. A normality study will be conducted and further descriptive statistics will be carried out. The Shapiro-Wilk test will be used to test whether the data conform to a normal distribution. If the parameters are normally distribution, the one-way ANOVA test will be used to compare the three groups, the independent t-test will be used for two groups comparison, and the Paired t-test will be used to compare the results before and after training within the group. If the parameter is Non-normally distribution, the Kruskal Wallis test will be used to compare the three groups, the Mann-Whitney u test will be used for two groups comparison, and the Wilcoxon rank test will be used to compare the results before and after training within the group. The level of statistical significance will be set at  $p < 0.05$ .

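### The trial is sized for one test at 5% on blood lipids, but eight variables are primary and each is tested at p < 0.05, so the stated alpha does not describe the decision rule

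*Protocol*

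**What the plan says.** Section 3.3 (Sample size) begins its calculation from this premise: "Since blood lipids are the main outcome variable of the study". It chooses the one-way omnibus ANOVA in G*Power with f = 0.40, and for the error rate "err prob is set to 0.05"; for power and design, the "value is set to 0.80, Number of groups is set to 3". The output is 66 in total, 22 per group, later raised to 30 per group. No individual lipid is named.

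Section 3.7.1 (Primary outcome measures) has two headings of equal rank. The first is body composition: "Measures of body composition variables include: body weight, BMI, fat percentage, muscle content". The second is blood lipid: "Measures of blood lipid variables include: total cholesterol (TC), triglyceride (TG), low-density lipoprotein cholesterol (LDL-C) and high-density lipoprotein" cholesterol (HDL-C). That makes eight primary variables.

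Section 3.8.2 (Data analysis) gives one-way ANOVA or Kruskal-Wallis for three groups and the independent t-test or Mann-Whitney test for two groups. It closes with one rule for all of them: "The level of statistical significance will be set at" p < 0.05. It does not say how many pairs are tested, whether pairwise tests depend on the three-group result, or how eight primary results combine into a conclusion.

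Section 2 (Objectives) asks both whether each Tai Chi form has an effect and how the two forms compare, on physical fitness and on blood lipids. All three pairs of groups are therefore of interest.

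**The concern.** Sections 3.3 and 3.7.1 do not describe the same primary endpoint. A reader of 3.3 expects the trial to be judged on lipids. A reader of 3.7.1 may accept a difference in weight, BMI, fat percentage or muscle content as a primary success. Even under 3.3 alone, blood lipids are four variables rather than one.

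The sample size calculation attaches a 5% error rate to one F test on one variable. If any of eight variables, or any of three pairs on any of them, can support a positive conclusion, the chance of a false claim is well above 5%. The choice of which result to present as the main one would also be open after the data are known.

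**Working it through.** **Inputs from the protocol.** Three groups, 1:1:1 (section 3.1.1); f = 0.40, alpha 0.05, power 0.80 (3.3); 30 per group planned (3.3); eight primary variables (3.7.1); p < 0.05 for every test (3.8.2).

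**Assumed.** The protocol gives no correlations between the outcomes. A common correlation from 0 to 0.7 is used. All error rates below are under the global null, meaning no difference between groups on any variable.

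**Step 1: reproduce the stated sample size.** The noncentrality is λ = f² × N = 0.16 × 66 = 10.56, with 2 and 63 degrees of freedom. The critical F is 3.1428 and power is 0.8181. N = 63 gives 0.798, so 66 is the smallest balanced total that reaches 0.80. The stated figures are reproduced exactly. The same test has power 0.926 at N = 90.

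**Step 2: eight F tests, independent outcomes.** 1 − 0.95⁸ = 1 − 0.663 = 0.337. For the four lipids alone, 1 − 0.95⁴ = 0.185.

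**Step 3: correlated outcomes and pairwise tests.** Simulation with 30 per group, normal data and 40,000 trials per scenario. The outcome is at least one p < 0.05 among the eight primary variables:

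| Common correlation | Any F test | Any of three ungated t-tests per variable |
|---|---|---|
| 0 | 33.7% | 64.8% |
| 0.3 | 30.5% | 59.5% |
| 0.5 | 25.7% | 51.5% |
| 0.7 | 19.9% | 40.8% |

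Two patterns with weight–BMI and TC–LDL-C strongly correlated gave 29.2% and 26.4% for any F test, and 57.2% and 52.9% for any ungated t-test. One variable with three ungated t-tests already gives about 12%. If t-tests are read only after a significant F test, the risk equals the F-test column. Treating all 24 pairwise tests as independent would give 1 − 0.95²⁴ = 70.8%, which is too high because the three pairs share groups.

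For the four lipids alone, from correlation 0 to 0.7, the range is about 19% down to 13% for any F test and about 41% down to 29% for any ungated t-test.

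**Step 4: power under the possible repairs, if f = 0.40 holds.**

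| Primary outcomes | Level per F test | Power at N = 66 | Power at N = 90 |
|---|---|---|---|
| One | 0.05 | 0.82 | 0.93 |
| Four lipids, Bonferroni | 0.05/4 = 0.0125 | 0.63 | 0.81 |
| All eight, Bonferroni | 0.05/8 = 0.00625 | 0.54 | 0.74 |

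**The case against.** The strongest reply is that section 3.8.2 is brief rather than wrong. It does not say that the tests are unadjusted, or that two-group tests run whatever the ANOVA shows. It names the three-group test first, which fits the usual order of omnibus test and then pairs. Gating and adjustment are often left to a statistical analysis plan, and that document is not at hand. This stands in part. The 40–65% range applies only if the pairs are ungated, so it should not be given as the error rate of the plan. The objection does not remove the 20–34% range, which applies even with a gate, or the contradiction between 3.3 and 3.7.1. An adjustment written elsewhere would not settle which outcome is primary, and an adjustment over eight variables would change the alpha used in 3.3.

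Three stronger readings are tempting, and the protocol does not support them:

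- **A single headline figure, such as over 50%.** This fails at a correlation of 0.7 (40.8%) and fails wherever pairs are gated.
- **Weight and BMI count one result twice.** With height nearly fixed over 12 weeks this is fair for changes within a person. Section 3.8.2 does not say that groups are compared on change. Across men of different heights within the narrow entry range for BMI, post-training weight and BMI are less closely tied.
- **The trial misses its stated 0.80 power.** It does not, for the test it sized: 0.82 at N = 66 and 0.93 at N = 90. The lower figures in step 4 describe adjustments that the protocol does not propose.

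Two primary domains are also not wrong in themselves. Section 2 gives physical fitness and lipids equal standing, so body composition need not lose primary status.

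**Conclusion.** The point holds. The protocol contradicts itself on the primary endpoint, and its alpha of 0.05 belongs to one F test, not to eight primary variables each tested at p < 0.05. The chance of at least one false-positive primary result is about 20–34% for the three-group tests or for gated pairs, and about 40–65% if pairs are ungated. On the narrower reading that only the four lipids count, it is about 13–19% and 29–41%. These ranges rest on the global null, normal data and assumed correlations from 0 to 0.7. They leave out the secondary outcomes and the within-group before–after tests. No correlation in that range brings the risk near 5%. The direction is therefore firm, while the exact size is not known.

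**What to change.** Before any outcome data are seen, make sections 3.3 and 3.7.1 name the same primary outcome or outcomes, by one of two routes:

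1. **One primary variable.** Name it exactly; if section 3.3 governs, it is one of the four lipids, and which one is for the investigators to decide. The other seven become secondary. Alpha 0.05 and the sized power stand (0.82 at N = 66, 0.93 at N = 90, if f = 0.40).
2. **Several primary variables.** Apply Holm across their three-group tests and restate the power for each. A Bonferroni split at N = 90 gives 0.81 over four lipids and 0.74 over eight; dropout from 90 lowers both.

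Under either route, state in section 3.8.2 that the pairwise contrasts for a primary variable are interpreted only if its three-group test is significant. With three groups this holds the error for that variable at 5%. It does not control error across variables, which is why route 2 also needs Holm.

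The cost is wording. Route 1 takes primary status from seven variables and needs no more participants. Route 2 keeps the breadth and pays in power, or in sample size: eight primaries under Bonferroni need 102 analysed (34 per group) for 0.80.
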